# Comparison of extended reality and conventional methods of basic life support training: protocol for a multinational, pragmatic, noninferiority, randomised clinical trial (XR BLS trial)

**DOI:** 10.1186/s13063-021-05908-z

**Published:** 2021-12-20

**Keywords:** Cardiopulmonary resuscitation, Basic life support, Virtual reality, Extended reality, Education

## Abstract

**Background:**

Conventional cardiopulmonary resuscitation (CPR) training for the general public involves the use of a manikin and a training video, which has limitations related to a lack of realism and immersion. To overcome these limitations, virtual reality and extended reality technologies are being used in the field of medical education. The aim of this study is to explore the efficacy and safety of extended reality (XR)-based basic life support (BLS) training.

**Methods:**

This study is a prospective, multinational, multicentre, randomised controlled study. Four institutions in 4 countries will participate in the study. A total of 154 participants will be randomly assigned to either the XR group or the conventional group stratified by institution and sex (1:1 ratio). Each participant who is allocated to either group will be sent to a separate room to receive training with an XR BLS module or conventional CPR training video. All participants will perform a test on a CPR manikin after the training. The primary outcome will be mean compression depth. The secondary outcome will be overall BLS performance, including compression rate, correct hand position, compression, and full release and hands-off time.

**Discussion:**

Using virtual reality (VR) to establish a virtual educational environment can give trainees a sense of realism. In the XR environment, which combines the virtual world with the real world, trainees can more effectively learn various skills. This trial will provide evidence of the usefulness of XR in CPR education.

**Trial registration:**

ClinicalTrials.gov NCT04736888. Registered on 29 January 2021

**Supplementary Information:**

The online version contains supplementary material available at 10.1186/s13063-021-05908-z.

## Introduction

### Background and rationale

In Europe and the USA, more than 300,000 cases of out-of-hospital cardiac arrest (OHCA) occur annually, and OHCA is a significant global health problem [1, 2]. To improve the outcomes of patients with OHCA, the early recognition of cardiac arrest and performance of cardiopulmonary resuscitation (CPR) by bystanders are the most essential steps. However, bystander CPR is provided to patients with OHCA in less than 50% of cases [3, 4]. Therefore, it is very important to provide CPR training to the general public.

Conventional CPR training consists of instructor-led in-person training after an online course. Although several feedback devices have been developed to improve the quality of the training, they were neither realistic nor immersive [5]. In addition, in conventional training programmes, trainees are constrained in terms of time and location, as they are usually kept to a schedule.

Virtual reality (VR) technology designed to maximise immersion has been shown to be able to overcome these limitation s[6]. Nas et al. reported a comparable chest compression rate but inferior compression depth with VR CPR training compared to conventional face-to-face training [7]. These results suggest that although VR has advantages over conventional education methods, it is difficult to perform techniques such as chest compression, ventilation, and defibrillation with real senses [8].

On the other hand, extended reality (XR), which combines the virtual and real worlds, could alleviate these shortcomings by using real manikins in a virtual environment, and consequently, it could be used to conduct realistic and immersive training without being constrained by space and time.

### Objectives

The aim of this study is to compare the efficacy of the XR-based basic life support (BLS) training method, which combines VR and the use of manikins, with that of the conventional training method. The hypothesis of this study is that the BLS skills gained by the XR method are not inferior to those gained by the conventional method.

### Trial design

This study is a prospective, multinational, pragmatic, noninferiority, randomised controlled study. Four institutions in 4 countries will participate in the study. The trial protocol will be approved by the Institutional Review Boards (IRBs) of the individual participating institutions (Fig. 1). This study was registered at ClinicalTrials.gov (National Clinical Trial (NCT) number: NCT04736888), and the protocol was designed following the guidelines of the Consolidated Standards of Reporting Trials and Standard Protocol Items: Recommendations for Interventional Trials (SPIRIT) (Supplementary file 1 SPIRIT 2013 checklist) (Fig. 2).

**Fig. 1 Fig1:**
[figure not shown]
Study algorithm. Q&A question and answer

**Fig. 2 Fig2:**
[figure not shown]
Schedule of enrolment, interventions, and assessments according to the Standard Protocol Items: Recommendations for Interventional Trials (SPIRIT) guideline. XR, extended reality; CPR, cardiopulmonary resuscitation; Test #1, hands-only CPR; Test #2, 5 cycles of 30 compressions and a 10-s rest

## Methods: participants, interventions, and outcomes

### Study setting

We designed a multinational, multicentre, randomised clinical trial that will include 154 participants from Seoul National University Bundang Hospital (South Korea), Children’s Hospital Los Angeles (USA), Royal Manchester Children’s Hospital (UK), and National University of Singapore (Singapore).

CBS 2.0™ (Tetra Signum, Inc., Seoul, South Korea), a self-learning type of XR solution, will be used for XR-based BLS training. A total of 154 participants will be enrolled after recruitment is announced, and a stratified permuted block will be used for randomisation. We plan to begin trial recruitment in March 2021, and the planned study period will be 6 months.

### Eligibility criteria

Individuals who are not healthcare providers and are 18 years old or older will be eligible for inclusion. Participants who are not capable of performing either the training or the CPR test due to physical or cognitive limitations will be excluded [7, 9–11]. Those who have upper extremity injuries or are pregnant will also be excluded [12]. If participants experience dizziness, headache, or motion sickness during the 2-min XR device adaptation period that prevents them from participating in the simulation study, they will also be excluded [13].

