**Fig. 3 Fig3:**
[figure not shown]
Extended reality basic life support module. **a** Components of the extended reality basic life support module. **b** The real-time chest compression feedback in virtual reality environment. **c** The real-time ventilation feedback in virtual reality environment

The VR-BLS training application was developed according to the 2020 AHA (American Heart Association) guidelines for BLS [7]. The learning mode consists of two parts: an introductory video explaining the CPR steps and a VR instructor explaining the steps in much more detail. Participants can perform techniques such as chest compression and ventilation on the mannequin in front of them even in a VR environment. The practice mode takes place in a street environment and has a VR instructor programmed to instruct participants to perform each step of CPR (Supplementary video). To adapt to the XR equipment, XR group participants are allotted an additional 2 min.

In both groups, BLS training will take approximately 60 min and is composed of checking responsiveness, calling for help, checking breathing, performing chest compressions, performing rescue breathing, and using a defibrillator. All training in both groups will be conducted by only one participant at a time.

Each group will be trained to perform both standard 30:2 CPR and hands-only CPR. Participants will be taught to use a face mask or cloth to cover the patient’s face and to perform hands-only CPR to reduce the risk of disease transmission when the patient is a suspected or confirmed or unknown case of COVID-19 [14, 15]. In addition, participants will also be taught to perform standard 30:2 CPR. The XR group will follow the instructions of the XR content, while the conventional group will watch the BLS video and follow its instructions [16]. Both groups will have a 5-min Q&A (question and answer) session after training (Fig. 1).

All participants and BLS instructors will wear a mask and follow social distancing guidelines to prevent the transmission of respiratory diseases during the study. There is no other specific relevant concomitant care and interventions that are permitted or prohibited during the trial.

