### Criteria for discontinuing or modifying the allocated interventions

During the study, those who experience dizziness, headache, motion sickness, or physical injuries that prevent their participation in this study will be excluded [13]. Participants may choose to discontinue their participation at any time for any reason.

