### Recruitment

Volunteers will be recruited through announcements published on the official website of each institution as well as via direct contact or email invitation. Participants will be enrolled competitively, but a minimum of 32 participants will be enrolled from each participating institution.

Regarding enrolment and allocation, once the participant informs the researcher of his or her intention to participate in the study through the website or email or directly to the researcher, the date will be coordinated with the researcher, and then informed consent will be obtained. After that, randomisation will be conducted. If there are not enough participants, the period will be extended to encourage voluntary participation.

Since this study is for nonhealthcare providers, nonhealthcare providers from each institution can all be potential participants. In case of significant delays in enrolment, we will visit the department where nonhealthcare providers work to inform them of the study objectives and encourage participation.

Furthermore, the possibility of self-selection bias exists, which causes those interested in CPR to participate in the study. However, considering that the primary outcome of this study is a comparison of chest compression depth between the two educational methods, self-selection bias may not cause significant bias in the interpretation of the results.

Recruitment will be completed once the required number of volunteers has been obtained. There will be no officially paid incentives to participate in this study, but small gifts may be provided depending on the institutional conditions.

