### Implementation

Researchers from each institution will enrol participants, and randomisation sequences will be performed with REDCap. After randomisation, the researcher will send the participants to room A (conventional group) and room B (XR group) according to the results of randomisation. Participants will receive corresponding training in each room.

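### The XR adaptation-period exclusion is listed under eligibility but can act only after randomisation and only in the XR arm, so it can bias the noninferiority comparison, most likely towards XR

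*Protocol article*

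**What the plan says.** Five places in the protocol article bear on this.

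- **Eligibility criteria** lists among the exclusions a rule that begins "If participants experience dizziness, headache, or motion sickness during the 2-min XR device adaptation period". The rule covers only symptoms severe enough to prevent participation, not every symptom.
- **Intervention description** gives the adaptation period to one arm: "To adapt to the XR equipment, XR group participants are allotted an additional 2 min".
- **Recruitment** fixes the order of events. A date is agreed, "and then informed consent will be obtained. After that, randomisation will be conducted".
- **Implementation** confirms that training rooms come later: "After randomisation, the researcher will send the participants to room A" or room B, according to the allocation.
- **Criteria for discontinuing or modifying the allocated interventions** has a broader rule: "During the study, those who experience dizziness, headache, motion sickness, or physical injuries that prevent their participation in this study will be excluded". This wording is neutral between arms and includes injuries.

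Adverse event reporting and harms adds that a participant whose adverse event prevents completion is withdrawn. Statistical methods tests noninferiority of mean depth with a one-sided 95% confidence interval against −5 mm. No section says whether people excluded for symptoms go on to test #1 or are kept in the primary comparison.

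**The concern.** An eligibility criterion is harmless to a randomised comparison when it is applied before allocation, because it then shapes both arms alike. Here the event that triggers it can happen only to someone already allocated to XR. A person in the conventional arm who would have reacted to the headset in the same way is never exposed to it and stays in. Followed literally, the plan compares XR participants who could continue with all conventional participants.

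What is at stake is the validity of the primary conclusion. Being unable to get through XR training is an unfavourable result of the method under test. In a noninferiority trial, removing such results from the experimental arm alone would be expected to move the estimate away from the margin and make a false claim of noninferiority more likely. An analysis plan could later declare that all randomised participants are analysed, but it could not recover a test #1 depth that was never measured because the person had been excluded.

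**Working it through.** **1. Order of events.** Consent, then randomisation (Recruitment), then dispatch to the training room (Implementation), then 2 minutes of adaptation for the XR group (Intervention description), then possible exclusion (Eligibility criteria). The figures are not shown, but nothing in the text puts device exposure before randomisation or gives it to the conventional group. So the rule acts after allocation and in one arm.

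**2. The plan's own sample size.** Inputs from Sample size: margin 5 mm, SD 10 mm, one-sided alpha 5%, power 90%, true difference taken as 0.

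n per group = 2 × 10² × (1.645 + 1.282)² / 5² = 68.5, rounded up to 69. Allowing for 10% drop-out, 69 / 0.9 = 76.7, rounded up to 77. Both stated figures are reproduced.

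**3. What the drop-out allowance does.** If 10% of the XR arm is lost, 77 × 0.9 = 69.3 remain against 77 controls, and power at a true difference of 0 with 69 against 77 is 91.5%. The allowance protects power. It does nothing for comparability.

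**4. Size of the bias.** Let q be the fraction of the XR arm excluded, and d the amount (mm) by which those excluded would have compressed less deeply than the XR participants who remain. Neither is in the documents, so both are assumptions. One anchor for d is the 5 mm gain from conventional training cited under Sample size.

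- XR mean over all randomised = retained XR mean − q × d, so bias towards XR = q × d.
- SE = 10 × √(1/[77(1 − q)] + 1/77).
- False noninferiority rate when the true all-randomised difference is −5 mm = Φ(q × d / SE − 1.645).

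For q = 5%, d = 5: bias 0.25 mm, SE = 10 × √(1/73.15 + 1/77) = 1.63, rate = Φ(0.153 − 1.645) = 6.8%.

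For q = 10%, d = 5: bias 0.50 mm, SE = 10 × √(1/69.3 + 1/77) = 1.66, rate = Φ(0.302 − 1.645) = 9.0%.

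| q | d (mm) | Bias towards XR (mm) | False noninferiority rate |
|---|---|---|---|
| 5% | −5 | −0.25 | 3.6% |
| 10% | −5 | −0.50 | 2.6% |
| 5% or 10% | 0 | 0 | 5.0% |
| 2% | 5 | 0.10 | 5.7% |
| 5% | 5 | 0.25 | 6.8% |
| 10% | 5 | 0.50 | 9.0% |
| 5% | 10 | 0.50 | 9.0% |
| 10% | 10 | 1.00 | 14.9% |

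**5. Sensitivity to the denominator.** With 69 analysed in each arm, SE = 10 × √(2/69) = 1.70 mm. For d = 5 mm the rates are 6.7% (q = 5%) and 8.8% (q = 10%). The conclusion is the same.

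**The case against.** The strongest reply is that direction and size are not in the documents. No section links susceptibility to headset symptoms with shallower compressions. If those excluded would have compressed as deeply as the rest, there is no bias; if deeper, the bias runs against XR. The rule also covers only symptoms that prevent participation, so the fraction may be small. All of this stands, and it is why the result is given as conditional.

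A second reply is that the article names no analysis population, which a separate analysis plan may properly define, and that the discontinuation section can be read as stopping participation rather than removal from analysis. This stands in part. The missing population is not the point here, and the arm-neutral discontinuation rule is not in itself a one-arm exclusion. But the adaptation-period rule is stated, sits under eligibility, and invites treating those affected as never validly enrolled. An analysis plan cannot supply outcomes that were not collected.

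A third reply is that some of those who stop may be unable or unwilling to be tested, so rewording alone leaves missing data. That is correct, and it is why the fix needs a sensitivity analysis as well.

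A reader might go further and infer that the rule conflicts with the trial's pragmatic label. That is an opinion about design, not a contradiction in the text, and the point does not depend on it.

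**Conclusion.** The structural flaw is established from the text: an exclusion presented as eligibility operates after randomisation and in the XR arm only, and no other section repairs it. It can bias the primary comparison, most likely towards XR, because those removed are people for whom XR training failed.

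The size rests on assumptions. With 5–10% of the XR arm excluded and a 5 mm shortfall, the bias is 0.25–0.5 mm, that is 5–10% of the margin, and false noninferiority at a true difference of −5 mm is about 7–9% instead of 5%. These rates assume SD 10 mm, normality and no other differential loss.

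A reader might infer that the trial is shown to favour XR, that any dizziness or headache leads to removal, or that the error rate reaches about 15%. The documents support none of these. The direction is expected rather than demonstrated, the rule is limited to symptoms that prevent participation, and the 15% figure needs 10% excluded and a 10 mm shortfall, which is a full SD and twice the cited training gain.

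**What to change.** Remove the adaptation-period symptom rule from Eligibility criteria as a post-randomisation exclusion. Reconcile Eligibility criteria, Intervention description, the discontinuation section and Recruitment so that stopping training is separate from exclusion from analysis. The stopping rule itself, including its cover for injuries, stays unchanged. Then state that:

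- all randomised participants remain in the primary analysis in their allocated group;
- those who stop XR training are invited to take test #1 if able and willing (the test uses a manikin, and no headset is described for it);
- symptom-related stops are reported by arm;
- a conservative sensitivity analysis covers missing test #1 depth, for example by setting missing XR values 5 mm below the conventional mean.

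The cost is protocol wording and one additional analysis; the required sample size does not change. The downside is that the XR mean may be slightly less favourable.

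Giving the adaptation check to every consenting person before randomisation would also restore symmetry. However, it would expose controls to the headset, could cause symptoms before their training, and would limit the results to people who tolerate XR.

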### Ethics approval

The investigators of each institution will explain to the participants the purpose of the study, the risks and benefits of the research, and how to contact the study investigators (or the Seoul National University Bundang Hospital ethics review board) regarding the problems that occurred in this study prior to obtaining their informed consent (Supplementary file 4 INFORMATION AND INFORMED CONSENT FORM).

## Interventions

### Explanation of the choice of comparators

Participants will be randomly assigned to (1) the XR group or (2) the conventional group stratified by institution and sex. Because an instructor-led in-person training course after an online course is the current standard CPR training method, the conventional group has been chosen as the control group.

### Intervention description

Participants will be randomly assigned to either the XR group or the conventional group (1:1 ratio). Each participant who is allocated to either group will be sent to a separate room (room A for the XR group and room B for the conventional group) and trained with an XR BLS module or conventional CPR training video.

Conventional CPR training consists of instructor-led in-person training with a BLS video and a manikin equipped with a feedback device. XR group participants, on the other hand, are trained through self-training using the XR BLS module without an instructor.

The XR BLS module features a housing unit with an attached base station, a touch screen that students can use to play content, a half-torso manikin (BestCPR, Gimpo, Korea), and an HTC Vive Pro Head-Mounted Display (HMD) with an attached hand tracking device (Leap Motion, UltraLeap, CA, USA) (Fig. 3).

**Fig. 3 Fig3:**
[figure not shown]
Extended reality basic life support module. **a** Components of the extended reality basic life support module. **b** The real-time chest compression feedback in virtual reality environment. **c** The real-time ventilation feedback in virtual reality environment

The VR-BLS training application was developed according to the 2020 AHA (American Heart Association) guidelines for BLS [7]. The learning mode consists of two parts: an introductory video explaining the CPR steps and a VR instructor explaining the steps in much more detail. Participants can perform techniques such as chest compression and ventilation on the mannequin in front of them even in a VR environment. The practice mode takes place in a street environment and has a VR instructor programmed to instruct participants to perform each step of CPR (Supplementary video). To adapt to the XR equipment, XR group participants are allotted an additional 2 min.

In both groups, BLS training will take approximately 60 min and is composed of checking responsiveness, calling for help, checking breathing, performing chest compressions, performing rescue breathing, and using a defibrillator. All training in both groups will be conducted by only one participant at a time.

Each group will be trained to perform both standard 30:2 CPR and hands-only CPR. Participants will be taught to use a face mask or cloth to cover the patient’s face and to perform hands-only CPR to reduce the risk of disease transmission when the patient is a suspected or confirmed or unknown case of COVID-19 [14, 15]. In addition, participants will also be taught to perform standard 30:2 CPR. The XR group will follow the instructions of the XR content, while the conventional group will watch the BLS video and follow its instructions [16]. Both groups will have a 5-min Q&A (question and answer) session after training (Fig. 1).

All participants and BLS instructors will wear a mask and follow social distancing guidelines to prevent the transmission of respiratory diseases during the study. There is no other specific relevant concomitant care and interventions that are permitted or prohibited during the trial.

### Test procedure

All participants will take a test at least 10 min after completing the training [10, 11]. The test will be conducted by a BLS instructor who has not been involved in BLS training. The Laerdal Resusci Anne™ manikin (Laerdal Medical Corporation, Stavanger, Norway) will be used. Additionally, depending on the policies of each participating institution, the test will be recorded on a smartphone, video camera, or other recording devices after obtaining consent from the participant.

The test will consist of two parts. Each part will assess the CPR steps of ‘checking for a response’, ‘calling for help’, ‘checking for breathing’, ‘performing chest compressions’, and ‘using an automated electrical defibrillator (AED)’. This study’s main test, test #1, will use hands-only CPR as the primary assessment criteria and will be conducted in line with the American Heart Association (AHA) and European Resuscitation Council (ERC)’s ‘Basic life support guidelines for adults with suspected or confirmed COVID-19’.

Test #2 will assume a scenario in which the patient is not suspected of having COVID-19 and will assess BLS skills with the 30:2 chest compression to rescue breath ratio. However, as face shields and pocket masks do not guarantee protection from the transmission of COVID-19 between the participants via a manikin, the rescue breaths will be substituted by a 10-s rest. To reduce interference between the two tests, after the continuous chest compression assessment (test #1), the assessment of 5 cycles of 30 chest compressions with a 10-s rest between each cycle as a substitute for rescue breaths (test #2) will be conducted after a 10-min break. To evaluate the effectiveness of BLS training, a Laerdal Resusci Anne™ manikin connected to the Laerdal SimPad SkillReporter™ will be used. All records stored on the Skillreporter™ will be analysed on a computer equipped with the Laerdal PC Skill Reporting System (Laerdal Medical Corporation). After the test, all participants will be asked to fill out a questionnaire.

